### Sample size and power calculations

The study will be longitudinal, with participants followed over a 12-month period. Psychological distress will be assessed using the SRQ-20, with a score of 6 or higher indicating distress. The primary outcome of interest will be remission of distress, defined as an SRQ-20 score below 6. All participants enrolled at baseline will have a level of distress. The intervention is hypothesised to reduce distress prevalence by at least 25%.

Given the longitudinal design and the use of clinic-based interventions, clustering effects will be accounted for by applying a design effect of 1.2, which reflects improved clustering control. Statistical parameters will include a confidence level of 95%. The total sample size will be fixed at 1,000 participants, requiring adjustments to the effective sample size to account for clustering.

The power calculation will be performed using a z-test for two proportions to compare the baseline and post-intervention prevalence of distress.

Using the assumed 25% absolute reduction in distress prevalence, the adjusted effective sample size of 1,000 participants, and a two-tailed significance level of 0.05, the estimated power of the study is calculated to be 94.5%.

Given the 12-month follow-up period and the community-based nature of the intervention, we anticipate an attrition rate of approximately 15%, based on evidence from similar longitudinal studies in rural Ugandan settings. Despite the anticipated attrition, the study will maintain the recruitment target at 1,000 participants, acknowledging that some loss to follow-up is expected. The analysis will account for missing data through multiple imputation techniques and sensitivity analyses to ensure that the study maintains sufficient power and validity to detect the hypothesized effect size.

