
The Ebola +D mental health intervention will be implemented at 11 public health care facilities (health centre IIIs and IVs) in Mubende District. The intervention will be delivered by the health centre based medical team, in collaboration with members of the village health team (VHT), who constitutethe first level of the Ugandan health care system. At each facility, the intervention will be coordinated by a designated mental health contact person,either a general nurse or general clinician based at the health facility, and will be supported by mental health professionals from Mubende Regional Referral Hospital. The delivery team at each site will comprise two trained lay health workers (selected from the VHT), a supervisor (selected from the health centre staff), two clinicians from the health centre, and a visiting specialist mental health worker (psychiatric clinical officer or psychiatric nurse) affiliated with Mubende Regional Referral Hospital.

A health centre III is a key part of Uganda’s decentralised healthcare system, providing outpatient, maternal and child health, inpatient care, laboratory, and HIV/AIDS services at the sub-county level. Staffed by clinical officers, nurses, midwives, and lab technicians, it features a maternity ward, inpatient ward, outpatient department and a laboratory. It serves as a referral point for health centre II facilities and collaborates with Village Health Teams to promote public health and preventive care. A health centre IV in Uganda is a higher-level facility within decentralised health care system, serving as the sub-district’s main health unit. It provides comprehensive outpatient and inpatient care, including advanced maternal and child health services, emergency obstetric care, and minor surgical procedures. It acts as a referral point for health centre III facilities. It is staffed by a medical officer, clinical officers, nurses, midwives, laboratory technicians, and support staff.

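### The sample-size section calls 1,000 both the fixed total and the size after a design effect of 1.2, and its 94.5% power does not follow from its own inputs

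*Protocol article*

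**What the plan says.** All the figures are in the Protocol article, *Sample size and power calculations*, unless noted.

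- **Clustering:** it is handled by "applying a design effect of 1.2, which reflects improved clustering control". No intracluster correlation (ICC) is given.
- **Total:** "The total sample size will be fixed at 1,000 participants, requiring adjustments to the effective sample size to account for clustering".
- **Power:** the test is a two-proportion z-test of distress prevalence at baseline against post-intervention. It is worked out "Using the assumed 25% absolute reduction in distress prevalence", with "the adjusted effective sample size of 1,000 participants" and "a two-tailed significance level of 0.05". The result is given as 94.5%.
- **Baseline:** "All participants enrolled at baseline will have a level of distress". Eligibility requires an SRQ-20 score of 6 or more, and remission is a score below 6.
- **Attrition:** about 15% is expected over 12 months. Recruitment stays at 1,000, and the plan relies on "multiple imputation techniques and sensitivity analyses to ensure that the study maintains sufficient power".
- **Sites:** "The Ebola +D mental health intervention will be implemented at 11 public health care facilities" (*Ebola+D mental health intervention*). *Participants and procedure*, item 3, sets a target of at least 100 enrolled at each of them.

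**The concern.** A design effect turns a number of participants into a smaller effective number. Here the same 1,000 appears on both sides of that conversion, so the adjustment was announced but not made. The attrition rate is stated but is not carried into the effective size or the power.

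The power figure also looks implausible on its face, because a 25-point difference with 1,000 observations per occasion is not a close call. The design effect is small for clusters of about 90 people.

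This section is the plan's only statement of how much information the study will yield on its primary outcome, remission. If its effective size is wrong and its power cannot be reproduced, readers have no reliable guide to the precision of the result.

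**Working it through.** **Inputs from the protocol.** Total 1,000; design effect (DE) 1.2; attrition 15%; 11 facilities; at least 100 per facility; 25-point absolute reduction; two-sided 0.05; stated power 94.5%. The baseline proportion is 100% by eligibility, which makes the follow-up proportion 75%. Since the section does not print the two proportions, the least favourable pair 25 points apart (62.5% and 37.5%) is checked as well.

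**1. The stated power.** With n per occasion, d = p1 − p2 and p̄ the mean of the two proportions, power = Φ{[d√n − 1.96√(2p̄(1−p̄))] / √(p1(1−p1) + p2(1−p2))}.

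- 100% to 75%, n = 1,000: (0.25 × 31.62 − 0.917)/0.433 = 16.1, so power is effectively 100%.
- 62.5% to 37.5%, n = 708: (0.25 × 26.61 − 1.386)/0.685 = 7.7, effectively 100%.
- 62.5% to 37.5%, with the 708 split into two halves of 354: (0.25 × 18.82 − 1.386)/0.685 = 4.8, above 99.9%.

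Solving the same formula for 94.5% gives n of about 42 per occasion (100% to 75%) to 99 (62.5% to 37.5%). The stated power is not reproduced with the stated inputs.

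**2. Effective size.**

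| Total | Total / 1.2 | After 15% attrition, / 1.2 |
|---|---|---|
| 1,000 | 833 | 850/1.2 = 708 |
| 1,100 (11 × 100) | 917 | 935/1.2 = 779 |

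**3. ICC implied by the design effect.** DE = 1 + (m − 1) × ICC. With m = 1,000/11 = 90.9, ICC = 0.2/89.9 = 0.0022. With m = 100, it is 0.2/99 = 0.0020.

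**4. Why power is the wrong yardstick.** With the baseline fixed at 100%, the same formula reaches 94.5% power for a fall of only about 1.3 points at n = 1,000, or 1.8 points at n = 708. Almost any remission would be significant, so power says little about what the study can show.

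**5. Precision of the remission proportion.** The ICC values are an assumed range, because the protocol gives none. With 850 completers over 11 facilities, m = 77.3. The effective size is 850/DE, and the 95% half-width at 50% remission is the multiplier × √(0.25/effective n). The multiplier is 2.228 (t, 10 df) or 1.96 (z).

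| Assumed ICC | DE | Effective n | Half-width, t | Half-width, z |
|---|---|---|---|---|
| 0.01 | 1.76 | 482 | 5.1 points | 4.5 points |
| 0.02 | 2.53 | 337 | 6.1 points | 5.3 points |
| 0.05 | 4.81 | 177 | 8.4 points | 7.4 points |

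For comparison, an effective 1,000 gives 1.96 × √(0.25/1,000) = 3.1 points. On the same z multiplier, the half-widths in the table are √(1,000/482) = 1.4, √(1,000/337) = 1.7 and √(1,000/177) = 2.4 times as wide. A small part of this is attrition: √(1,000/850) = 1.08.

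**The case against.** **This is a pilot seeking preliminary evidence, and the article condenses a longer protocol.** A source for the design effect may well be in that document, so the absence of a citation is not itself the fault. The fault is that the article prints figures that contradict each other, and a longer document cannot reconcile them.

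**Attrition is not ignored.** This is correct. The rate is disclosed, the decision to keep 1,000 is explicit, and imputation and sensitivity analyses are planned. Imputation can also recover some information from other assessments. What remains is narrower: the effective size and power do not reflect the loss, and imputation does not by itself guarantee power.

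**The 94.5% may come from another calculation.** A 25% relative reduction from a 50% baseline (50% to 37.5%), in two groups of about 417 (833/2), gives 95.5%. That needs a baseline the section does not state. It also contradicts both the absolute reduction and the 100% baseline that it does state.

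**A small design effect might be right.** It cannot be ruled out. However, each facility has its own two lay workers, supervisor and two clinicians, plus a visiting specialist, and the lay workers deliver the psychoeducation and problem-solving therapy. Some similarity of outcomes within a facility is plausible, and the section names no design feature that would reduce it.

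**Conclusion.** The section is wrong as written on two figures. The effective size is 833, not 1,000, and 708 after attrition (917 and 779 if the total is 1,100). The power implied by the stated inputs is above 99.9%, not 94.5%, both before and after those corrections.

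A reader might infer that leaving out the design effect and attrition inflated the power, or that the study is too small to detect 25 points. The documents support neither. The omissions do not explain the 94.5%, which is lower than the plan's own inputs give. Even at an assumed ICC of 0.05, with 850 completers per occasion and the least favourable proportions, power is 99.8%. It drops below 94.5% within the assumed range only if the completers are also treated as two halves (92.0% at ICC 0.05).

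The practical consequence is for precision. Under the assumed ICCs of 0.01 to 0.05, the half-width for 50% remission is about 4.5 to 7.4 points with z, or 5.1 to 8.4 with t on 10 df, against 3.1 for an effective 1,000. This rests on equal facility sizes, 15% loss at the assessment concerned, and an ICC range that is not taken from the protocol. Loss at 3 months may be smaller.

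**What to change.** In *Sample size and power calculations*:

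1. Reconcile the total of 1,000 with the target of at least 100 at each of 11 facilities, and state one figure.
2. Replace the effective size of 1,000 with 833 (708 after attrition), or with 917 (779) if 1,100 is the total.
3. Remove the 94.5% and give instead the expected 95% confidence-interval half-width for the remission proportion. A recomputed power above 99.9% would be correct but would tell the reader nothing.
4. Show that half-width for a stated range of ICCs, for example 0.01, 0.02 and 0.05 as tabulated above, and say whether t or z is used. If 1.2 is kept, state the ICC behind it and its source.
5. Delete the clause saying that the design effect reflects better control of clustering, and the claim that imputation maintains power. Imputation can stay as the method for handling missing data.

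The cost is one rewritten paragraph and one reconciled recruitment target. These corrections do not in themselves require extra participants. The downside for the sponsor is that the stated effective size and precision become less favourable.

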**Fig 1 pone.0329591.g001:**
[figure not shown]
Ebola+D study flowchart.

Eligibility criteria for participating in this study: i) Community member of Mubende district staying within the catchment area of the PHCF; ii) 18 years and above, iv) able to communicate in either English or Luganda (local language spoken in the study region and the language into which the questionnaires will be translated), v) has a WHO SRQ-20 score of 6 and above.

Exclusion criteria: i) unable to engage with the research process for any reason that may include sensory impairment or cognitive impairment.

The study aims to enrol at least 100 respondents with psychological distress (SRQ-20 score ≥ 6) from each of the 11 participating PHCFs. Enrolled respondents will be provided with PST at bi-weekly sessions. Monthly assessments will be undertaken to monitor their level of psychological distress using the SRQ-20 until psychological distress scores have fallen to less than 6. A patient will be declared in remission if after completing their prescribed therapy (PST or medication) they remain symptom free (SRQ-20 scores of less than 6) on two occasions one month apart. A full complement of supporting and resource materials including clinic posters, health worker aide-memoire, and patient and care-giver resource materials will be developed and evaluated. The reporting of the trial will be in accordance with the SPIRIT guidelines for interventional trials [40] (S1 File).

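### The stated 94.5% power does not follow from its inputs, and a baseline-versus-follow-up z-test cannot size a cohort that is 100% distressed by eligibility

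*Protocol article*

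**What the plan says.** All of this is in the protocol article. The eligibility criteria, under the third study objective, require that a participant "has a WHO SRQ-20 score of 6 and above". The section on sample size and power uses the same threshold for the outcome: "Psychological distress will be assessed using the SRQ-20, with a score of 6 or higher indicating distress". It adds: "All participants enrolled at baseline will have a level of distress". The primary outcome is the complement of distress: "The primary outcome of interest will be remission of distress, defined as an SRQ-20 score below 6".

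Power rests on one comparison: "The power calculation will be performed using a z-test for two proportions to compare the baseline and post-intervention prevalence of distress". The inputs are a 25-point effect ("Using the assumed 25% absolute reduction in distress prevalence"), an effective sample size printed as 1,000, and "a two-tailed significance level of 0.05". The stated result is 94.5%. The same section fixes recruitment at 1,000, names a design effect of 1.2, expects about 15% attrition and does not inflate recruitment for it. It gives no comparator and no rate of remission without treatment.

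**The concern.** There are two problems.

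- **The contrast.** Baseline prevalence is set by the entry rule and has no sampling variation. Comparing it with follow-up prevalence tests the null hypothesis that nobody scores below 6 later. Natural recovery, or ordinary fluctuation around a cut-off used for selection, could overturn that null with no treatment effect. The two proportions also come from the same people, whereas the two-proportion z-test assumes independent samples.
- **The number.** With the inputs as printed, power should be indistinguishable from 100%. A figure of 94.5% suggests that different inputs were used.

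At stake is the only quantitative justification given for the study's size. The section relies on it when it leaves recruitment uninflated for attrition and says that power will remain sufficient.

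**Working it through.** **Inputs from the article:** p1 = 1.00 (eligibility); p2 = 0.75 (25-point fall; from a 100% baseline, a relative 25% fall is the same thing); two-sided alpha 0.05; 1,000 recruited; design effect 1.2; attrition 15%.

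**Sample sizes after adjustment:** 1,000/1.2 = 833. With attrition, 850 are assessed, and 850/1.2 = 708. An effective n of 1,000 would need 1,000 × 1.2 = 1,200 recruited.

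**Attempt to reproduce 94.5%.** With n per time point and p̄ = (p1 + p2)/2 = 0.875:

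power = Φ{ [ (p1 − p2) − 1.96·√(2p̄(1 − p̄)/n) ] / √( [p1(1 − p1) + p2(1 − p2)]/n ) }

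Here 2p̄(1 − p̄) = 0.21875 and p1(1 − p1) + p2(1 − p2) = 0.1875.

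- n = 1,000: (0.25 − 0.0290)/0.01369 = 16.1, power 1.000
- n = 833: (0.25 − 0.0318)/0.01500 = 14.5, power 1.000
- n = 708: (0.25 − 0.0345)/0.01627 = 13.2, power 1.000
- n = 42: (0.25 − 0.1415)/0.0668 = 1.62, power 0.948
- n = 41: power 0.943

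So 94.5% would need only about 42 people per time point.

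**Variants tried:**

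- Sample split in half (500, 417, 425 or 354 per time point): 1.000.
- Arcsine effect size (n = 417 to 1,000): 1.000.
- Exact paired McNemar test (n = 708 to 1,000): 1.000.
- Other baselines from 25% to 100% with a 25-point fall: the least favourable is 62.5% to 37.5%. At n = 708 this gives (0.25 − 0.0521)/0.0257 = 7.7, power above 0.9999999. Even at n = 354 it is 0.999999.

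No baseline with the stated absolute fall gives 94.5% at any of these sizes.

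**What the contrast tests.** With baseline at 1,000/1,000 and x remitters, z = (x/n)/√(2p̄(1 − p̄)/n).

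- x = 3: p̄ = 0.9985, z = 0.003/0.001731 = 1.73, p = 0.083
- x = 4: p̄ = 0.998, z = 0.004/0.001998 = 2.00, p = 0.045

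Four remitters (0.4%) are enough. On this contrast, 94.5% power is reached at a fall of 1.25 points with n = 1,000, or 1.5 points with n = 833.

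**Precision of the remission proportion.** At 25% remission, the half-width is c·√(0.25 × 0.75/n_eff), with c = 1.96 (z) or 2.228 (t on 10 df, for 11 facilities).

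- Design effect 1.2, n_eff 708: standard error 0.01627, half-width ±3.2 points (z) or ±3.6 (t).
- Assumed ICC 0.01, 850/11 = 77.3 per facility: design effect 1 + 76.3 × 0.01 = 1.76, n_eff 482, half-width ±4.4 (t).
- Assumed ICC 0.05: design effect 1 + 76.3 × 0.05 = 4.81, n_eff 177, half-width ±7.3 (t).

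The article states no ICC. With 1,000 people in 11 facilities, a design effect of 1.2 corresponds to 0.2/(1,000/11 − 1) = 0.0022.

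**The case against.** The strongest reply is that the z-test is only a device for the power calculation. That stands: the section names it for nothing else. The data analysis section describes comparisons of mean scores at baseline, 3 and 12 months, and random effects logistic models for remission, relapse and recovery. A statistical analysis plan that is not shown may define the primary analysis. A reader might infer that the trial's planned analysis is empty and a positive result guaranteed. That would follow only if this z-test were also the outcome test, which the article does not say.

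A second reply is that the result is still informative. That also stands. With baseline at 100%, the fall in prevalence is the remission proportion, and its estimate and interval bear directly on the hypothesised 25 points. It is the null hypothesis of no remission that is uninformative.

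A third is that the error understates power and so does no harm. The first half is right, and the study is not shown to be too small. But near-certain power against a null that four remitters overturn does not justify the study's size.

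Nor can this be put down to condensation in a journal article. The test, effect, sample size, alpha and power are all printed, and they disagree.

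**Conclusion.** The point holds as a fault in the sizing statement. Baseline prevalence is 100% by construction, so the two-proportion contrast is an unsuitable basis for sizing. The article's own inputs give power of essentially 100% at n = 1,000, 833 and 708, not 94.5%. The effective sample size of 1,000 also contradicts the design effect of 1.2, which gives 833. These conclusions use only figures in the article.

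Two stronger readings are not supported: that the study is underpowered, and that its outcome analysis is invalid. It is also possible to find inputs that return about 94.5%, such as a relative 25% fall from about 27% at n = 1,000. They contradict the stated cohort, so they do not establish where the figure came from.

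The precision figures rest on further assumptions: 25% remission, 850 assessed, roughly equal facility sizes and, for the wider intervals, ICCs of 0.01 to 0.05.

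**What to change.** Delete the 94.5% and the two-proportion justification. State instead the expected 95% interval half-width for the proportion in remission, after design effect and attrition, and say which reference distribution is used. With effective n of about 708 and 25% remission this is about ±3.2 points with z, or ±3.6 with t on 10 df. Show the range for plausible ICCs as well, about ±4.4 to ±7.3 with t on 10 df for 0.01 to 0.05. Correct the effective sample size to 1,000/1.2 = 833 before attrition and about 708 after it.

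Power against a prespecified background remission rate may be added if the sponsor can justify one. It is optional: the article gives no such rate, and making it a success criterion would change the design of a pilot.

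The cost is one rewritten section and a short calculation, with no extra participants or visits.

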#### 4) To examine the costs of the Ebola + D mental health intervention.

A subset (n = 6) of the Ebola +D study facilities will be selected for the provider costing using a multi-stage stratified random sampling approach based on facility level and catchment population. We will estimate the average total unit cost per patient for screening and treatment of mental health disorders at the health facilities in Mubende district. A combination of retrospective and prospective methods of cost data collection will be used. Both macro (top-down) and micro (bottom-up) costing approaches will be applied. The disaggregated provider costs will be summed to produce a unit cost per patient for screening and treatment of mental health problems from the provider perspective.

#### 5) To explore the Ebola virus disease (EVD) associated negative beliefs and lived out experiences of affected members of the community.

A qualitative sub-study will be undertaken to explore the Ebola virus disease (EVD) associated negative beliefs and lived out experiences of affected members of the community. Fifty-nine (59) participants will be purposively sampled and stratified by gender from different categories of community members: patients/survivors (n = 15); suspected cases who were kept in the Isolation Unit (n = 5); family members of survivors and those who lost lives (n = 15); community members (including opinion leaders and traditional healers) (n = 8), health workers (n = 8); and (iv) volunteers (n = 8). The interviews will elicit participants’ perspectives on their experience living through the EVD epidermic, how it affected them psychosocially, how they coped with the psychosocial challenges and their continued psychosocial needs.

### Data collection, management, and analyses

#### i) To adapt the HIV + D collaborative stepped care mental health intervention to produce the Ebola+D mental health intervention.

Data will be collected from a number of sources, including case notes and transcripts from the audio recordings of the ToC workshops, existing documentation from the Ministry of Health department of Mental Health and Substance Use as well as minutes of the Ebola+D research meetings with Mubende health officials. For the qualitative data collected, content analysis will be undertaken after coding the transcripts; with the coding categories directly derived from the content of transcripts, without imposing any preconceived theoretical perspectives. A Qualitative data analysis software (nVivo_14_) will be used to aid the data analysis process.

